# **STATISTICS AND DATA ANALYSIS**

- 1. **Sample Size Calculation**

The sample size calculation was based on the analysis of the change in the primary outcome (VO_2peak_) at 10 weeks post-AF ablation from baseline. Previous studies investigated VO_2peak_ at 6 months post-ablation, which we assume to be similar at 10 weeks post-ablation. Based on Kato *et al.*, we can assume that the VO_2peak_ standard deviation is around 3ml/kg/min at baseline and 4ml/kg/min at 10 weeks post-ablation (63). As the correlation between the time points is unknown, we assume a value of r=0.5. Consequently, the standard deviation of the difference from 10 weeks post-ablation to baseline is around 3.6ml/kg/min. Based on Fiala *et al.* we can assume that the change in VO_2peak_ will be around 2ml/kg/min due to AF ablation and a further 4ml/kg/min (63,64) due to cardiac rehabilitation (which comprises pre- and post-AF ablation rehabilitation). Therefore, the difference between the intervention arm and standard care is expected to be 4ml/kg/min at 10 weeks (±2 weeks) post AF ablation compared with baseline. To detect a conservative difference of 2.5ml/kg/min (an increase in 2.5ml/kg/min VO_2peak_ in the intervention arm from standard care, at 10 weeks post-ablation compared with baseline) at 5% significance level, with 90% power, we require 88 patients in total. To allow a drop-out rate of 20%, we will recruit 106 patients, with 53 randomly allocated to each group.

- 1. **Planned Recruitment Rate**

Participants who are referred for first-time AF ablation at UHCW NHS Trust with AF symptoms and meet the remaining inclusion/exclusion criteria will be eligible for the study. At UHCW we are seeing ~300 patients each year at UHCW for first-time AF ablation and it is predicted that ~200 of these patients will be eligible. We will be aiming to recruit around 1-3 patients per week over an ∼16-month period to recruit the participant population within the ∼16-month recruitment period.

- 1. **Statistical Considerations**

All the scoring of HRQoL (EQ-5D-5L, SF-36 and AFEQT) will be computed as per the instrument algorithm. The scores will then be summarised descriptively overall and by treatment arms at baseline and the short- and long-term follow-up time points. The change of HRQoL from baseline to 10-week, from baseline to 12-month post-ablation, and the difference between treatment arms will be estimated with their associated 95% confidence intervals (CIs). We may explore the longitudinal effect of long-term HRQoL (12-month post-ablation). Proportion of significant AF event by treatment arms will be estimated with associated 95% CI using Kaplan-Meier. Similarly, the proportion of individual and composite MACE and its associated 95% CI by treatment arms will be estimated. The recurrence of AF burden from the Holter and each of the MACE occurrence will also be estimated by treatment arms as a time-to-event estimand. We will also perform a subgroup analysis by types of AF (persistent and paroxysmal AF) for all endpoints. We may also explore for any potential confounders in VO_2peak_ within the study, and the complier averaged causal effect (CACE) analysis as a sensitivity analysis.

- 1. **Procedure(s) to account for missing or spurious data**

We will endeavour to collect all data possible from each participant during their enrolment in the study. Data monitoring will be carried out by the trial manager/researcher and any missing data points will be raised as a query on the online database which will be followed up by the delivery team. If it is judged that the same critical data points (as outlined in the data management plan) are consistently being missed (>10%) then this will be raised at the following TMG for corrective action.

Multiple imputation methods will be used as secondary analysis if more than 10% of the outcome variable is missing.

- 1. **Economic Evaluation**

To assess the costs, benefits, and overall cost-effectiveness of the intervention, we will integrate a prospective economic evaluation into the trial. The time horizon of the analysis will be one year, congruently with the duration of the trial. The primary perspective will be NHS and Personal Social Services (PSS), with secondary analyses including additional patient costs accruing over the 12 months period post ablation.

Resource use and costs

Intervention resource use and costs associated with implementing and delivering the intervention will be captured within the trial. For example, for both arms we will record and then cost the AF cryoballoon and radiofrequency ablation procedure using published costing resources such as the NICE reference costs (40,41). For the intervention arm we will additionally record and cost the resource use associated with attendance to the pre- and post-AF ablation rehabilitation intervention components. Further use of other NHS care (e.g. primary care appointments, outpatient visits, inpatient admissions) and related costs incurred by the patient (e.g. out-of-pocket expenses and time-related costs) will be captured using a resource use measure (RUM) at different points in time. To cost the intervention and healthcare resource use, we will apply unit costs using national reference sources, e.g., PSSRU (65). This will allow the calculation of total healthcare costs related to AF from baseline to 12 months for both arms of the trial including those attributable to the intervention.

Outcomes

Responses to EQ-5D-5L, a widely used preference-based quality of life instrument, collected at baseline and follow-up visits will be used to calculate quality-adjusted life years (QALYs) using UK value set recommended by NICE at the time of the analysis. Similarly, responses to the SF-36 questionnaire will be used to derive preference-based quality of life indices through the SF-6D algorithm (66). Baseline utility scores will be used both in the construction of QALYs and as an adjusting covariate within the regression analysis. Mechanisms of missingness of data will be explored, and multiple imputation will be used if missing data is prevalent.

Analysis

The analysis will be conducted on an ‘intention to treat’ basis. Missing data will be accounted for by using appropriate techniques, such as multiple imputation, depending on the extent and type of missing items. As the distribution of cost is usually skewed by the existence of patients with very high costs, the calculated mean per-patient cost will be given alongside confidence intervals obtained through non-parametric bootstrap methods (67). Incremental analysis will be undertaken to calculate the difference in costs and the difference in outcomes (QALYs) associated with the intervention. Results will be presented in the form of incremental cost-effectiveness ratios (ICER), reflecting the extra cost for an additional unit of outcome. Sensitivity analyses will be undertaken to assess the impact of different assumptions on the results (68). To account for the inherent uncertainty due to sampling variation, the joint distribution of differences in cost and outcomes (QALYs) will be derived by carrying out a large number of non-parametric bootstrap simulations (69).

The simulated cost and outcome pairs will be depicted on a cost-effectiveness plane and will be plotted as cost-effectiveness acceptability curves (CEACs) (70). CEACs will show the probability of CREED AF being cost-effective across a range of possible values of willingness to pay for an additional QALY.

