|  | To explore if CREED AF intervention has an impact on the short- and long-term recurrence of AF post-ablation and the need for redo-AF ablation. | AF recurrence and burden from data collected from a 1–7-day(s) cardiac Holter monitoring at 10 weeks (±2 weeks) and 12 months (±4 weeks) post ablation, and requirement for redo-AF ablation as documented in medical records reviewed at 12 months post-ablation. |
|  | To explore the impact of CREED AF intervention on relevant major adverse cardiovascular events (MACE) in AF patients. | MACE at 12 months post-ablation, defined as:   1. Hospital admission related to AF 2. Non-fatal myocardial infarction 3. Non-fatal stroke 4. Cardiovascular death 5. All-cause mortality |

Key Words: **AF ablation, Pulmonary vein isolation, VO2peak**

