# **RATIONALE**

- 1. **Hypothesis**

It is hypothesised that the CREED AF intervention will improve key patient and health outcome measures, AF burden and physical activity in AF patients undergoing a first-time AF ablation only as their initial procedure, in line with current guidelines, compared to usual care.

- 1. **Justification**

Over the last few years our understanding of AF aetiologies and mechanisms has increased with the role of modifiable risk factors playing a significant role in AF progression and recurrence being increasingly recognised (31,42). While certain risk factors and predisposing conditions cannot be modified (such as age, ethnicity, gender, or genetic predisposition), several risk factors can be modified and optimally managed. These include: obesity, smoking, excess alcohol consumption, hypertension, diabetes, physical inactivity, and obstructive sleep apnoea. Many of these risk factors are like risk factors for other cardiovascular diseases such as ischaemic heart diseases, vascular disease, and heart failure. Patients suffering from these conditions are offered targeted integrated therapies which incorporate risk factor adjustment and management of lifestyle indices such as cardiovascular rehabilitation, as routine. However, current guidelines for patients undergoing AF ablation do not mandate referral for integrated therapies to provide management for these modifiable AF risk factors. Targeting these modifiable risk factors as early as possible in AF patients who have failed medical therapy could potentially reduce AF burden, reverse atrial remodelling and limit AF progression following an AF ablation procedure. It may also improve underlying co-morbidity and in turn reduce stroke and other cardiovascular adverse events.

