| To explore if the CREED AF intervention improves short- and long-term Atrial Fibrillation Effect on Quality-of-Life (AFEQT) in AF patients listed for first-time AF ablation compared to standard care. | The AFEQT is an AF-specific health-related QOL made up of 3 subscales (symptoms, daily activities, and treatment concern). The transformed overall score ranges from 0 (complete disability) to 100 (no disability).  Short-term: change of AFEQT from baseline to 10 weeks post-ablation.  Long-term: change of AFEQT from baseline to 12 months post-ablation. |
| To explore the cost-effectiveness of the CREED AF intervention compared to standard care. | The incremental cost per quality adjusted life year (QALY) will be estimated. See details in Section 10.7. |
| To explore if the CREED AF intervention can decrease AF burden and recurrences following AF ablation, and reduce the requirement for redo-AF ablation. This will be assessed with a 1–7-day cardiac Holter monitor at 10 weeks (±2 weeks) and 12-months (±4 weeks) post ablation, and on review of patients’ medical records at 12-months. | Participants will be fitted with a Holter monitor at the 10-week and 12-month post-ablation follow-ups. Of the list of summary data over the time period it is worn by the participant, only the significant AF event and burden, and when it occurred will be recorded. |
| To explore if the CREED AF intervention has an impact on major adverse cardiovascular events (MACE) at the 12-month follow-up between both groups. MACE will be defined as individual outcomes and as a composite of hospital admission related to AF, non-fatal myocardial infarction, non-fatal stroke, cardiovascular death, and all-cause mortality. | Any occurrence of the following events:   - Hospital admission related to AF (from hospital records) - Non-fatal myocardial infarction (as above) - Any non-fatal stroke (as above) - Cardiovascular death (as above) - All-cause mortality (as above)   and when each occurred. |

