The 1-to-1 education sessions in the CREED AF Intervention arm will be conducted by an exercise practitioner/researcher and will be performed either online, over the phone, or in-person. The sessions will incorporate comprehensive behavioural change and motivational strategies to improve patient adherence and compliance to risk factor modification with the aim of improving both short- and long-term adherence to exercise and lifestyle modification goals and reduce their exposure to lifestyle risk factors (e.g., smoking, alcohol consumption, weight reduction etc.). This will be guided by a participant workbook, and further sign-posting to support groups will be in accordance to individual participant’s requirements. A full compliance of education sessions is at least 2 sessions (of a total of 3; 66.7%) at each prehabilitation and rehabilitation intervention.

- 1. **Follow-up data**

In addition to cardiopulmonary exercise testing at 10 weeks follow-up post-ablation, all patients will also repeat the baseline questionnaires to assess their HRQoL, including the EQ-5D-5L, SF-36 and AFEQT, at significant intervals of the intervention journey (as outlined in the Schedule of Events). To assess for AF recurrence and burden, 7-day Holter ECG monitoring will be placed on patients at the 10 weeks and 12 months post-ablation follow-up appointments. The 10-week (±2 week) period will be seen as equivalent to a 3-month blanking period that is normally considered post-ablation in which presence of AF is not seen as a recurrence. The definition of an AF recurrence post-ablation will be an arrhythmia with the characteristics of AF that is either captured on a 12-lead ECG or documented to last for at least 30 seconds on ECG monitoring (1). At 12 months post-ablation, a retrospective review of medical records will be completed to collect data for study defined MACE. This will include, but will not be limited to, a review of clinic letters, medical coding, and A&E records.

- 1. **End of Study Definition**

The end of study definition will be when the last participant has completed their 12-month follow-up appointment and data collection post-ablation.

- 1. **Assessment and Management of Risk**

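### Section 10.5 gives AF burden only a time-to-event estimand, so the stated analysis does not estimate how much AF there is

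*Protocol*

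**What the plan says.** Burden and recurrence appear as two quantities. The Study Summary lists "AF recurrence and burden from data collected from a" 1- to 7-day Holter at 10 weeks and 12 months. The objective in Section 5 is "To explore if the CREED AF intervention can decrease AF burden and recurrences following AF ablation". The hypothesis in Section 3 is that "the CREED AF intervention will improve key patient and health outcome measures, AF burden and physical activity in AF patients".

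Burden is also collected. Section 5 says that, from the Holter summary for the period of wear, "only the significant AF event and burden, and when it occurred will be recorded".

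Section 10.5 (Secondary outcome analysis) then states two AF analyses:

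- "Proportion of significant AF event by treatment arms will be estimated with associated 95% CI using Kaplan-Meier"
- "recurrence of AF burden from the Holter and each of the MACE occurrence will also be estimated by treatment arms as a time-to-event estimand"

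The follow-up part of Section 9 defines recurrence as AF captured on a 12-lead ECG or "documented to last for at least 30 seconds on ECG monitoring".

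**The concern.** A time-to-event estimand answers whether AF came back and when. Burden asks how much of the monitored time was spent in AF. The objective asks both questions, and Section 10.5 attaches the first kind of answer to both. The phrase about recurrence of burden merges two quantities that the rest of the protocol keeps apart.

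At stake is the burden half of one secondary objective, which is also part of the trial hypothesis. A programme of exercise and risk-factor work could plausibly shorten AF without abolishing it. The stated analysis would not measure an effect of that kind. Leaving the choice of a burden measure until results are known would also invite selection among several possible summaries.

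**Working it through.** The protocol gives no figure for burden (no mean, SD or expected effect), so there is nothing to reproduce. The check compares outcome with estimand and adds simple arithmetic.

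**Step 1. Outcome against analysis**

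| Item in Sections 3 and 5 | Type of quantity | Analysis stated in 10.5 |
|---|---|---|
| AF recurrence | whether and when | Kaplan-Meier proportion; time-to-event |
| AF burden | how much | time-to-event only |
| Quality-of-life scores, for contrast | how much | change, and difference between arms, with 95% CI |

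The last row shows that 10.5 does state a between-arm difference where it intends to compare amounts. It states none for burden, and no other section does.

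**Step 2. What one event can stand for**

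Inputs: the 30-second threshold (Section 9, recurrence definition) and the recording length. Section 9 gives the length as 7 days: "7-day Holter ECG monitoring will be placed on patients at the 10 weeks and 12 months post-ablation follow-up appointments". The Study Summary, Schedule of Events and Section 5 give 1 to 7 days.

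- 7-day recording: 7 × 86,400 s = 604,800 s. Smallest qualifying burden = 30 / 604,800 = 0.0000496, about 0.005%. Largest = 100%. Ratio = 604,800 / 30 = 20,160.
- 1-day recording: 30 / 86,400 = 0.000347, about 0.035%. Ratio = 86,400 / 30 = 2,880.

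On this reading, a single 30-second episode and continuous AF throughout the recording each count as one event at the same visit.

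**Step 3. A higher threshold**

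The protocol does not define a significant AF event, so the threshold might be some burden level T above 30 seconds. All recordings from T to 100% would then score alike, a ratio of 100% / T. Raising T narrows the range, but magnitude above T is still not used.

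**Step 4. What the event analysis leaves out**

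Let p be the proportion with any AF in an arm and m the mean burden among those with AF. Mean burden in the arm is p × m. The event analyses carry information on p and on timing, but not on m. If p and timing are equal in the two arms, the event contrast is zero whatever m is, while mean burden differs by p × (m_intervention − m_control). The zero here follows from holding p equal. It shows what the estimand does not contain and says nothing about which effect is likely.

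**Step 5. Recording length**

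Continuous AF gives 24 hours of AF on a 1-day recording and 7 × 24 = 168 hours on a 7-day recording, yet 100% of monitored time on both. With recordings of 1 to 7 days, burden needs to be expressed per monitored time.

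**The case against.** The best defence is that the wording is loose. The time-to-event sentence may simply mean AF recurrence, and a statistical analysis plan could later define a burden summary. That is possible, but Section 10.5 would then give burden no analysis at all. Section 10.3 also says the analysis plan will elaborate the analyses that the protocol describes, and the one it describes for burden is time-to-event. The protocol has therefore gone beyond leaving a detail open: it has named a type of estimand that does not fit.

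The defence also notes that the objective is exploratory, is not part of the sample size calculation and has no bearing on the VO2peak conclusion. That stands and limits the severity. It is also right that a quantitative burden analysis will have low power and a wide interval in a trial of this size.

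A reader might infer several stronger things that the documents do not support:

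- **That a reduction in burden cannot be shown.** Section 5 has burden recorded, so it can be analysed. The limit applies to the stated analysis only.
- **That the 30-second rule certainly governs the event analysis.** That rule defines recurrence. Section 10.5 speaks of significant AF events and of recurrence of burden, and neither is defined.
- **That recording hours are not collected.** Section 5 takes the Holter summary over the period of wear. It does not say whether burden is held as a percentage or a duration, and the case report form is not shown.
- **That the trial would report no effect on burden.** A null time-to-event result would be a finding about recurrence.

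**Conclusion.** Wrong as written; minor. AF burden is a stated secondary outcome, separate from recurrence and recorded from the Holter, but the only estimand that Section 10.5 gives it is time-to-event. Followed literally, the plan never estimates the amount of AF.

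The size depends on an undefined term. If the 30-second definition applies, one event covers about 0.005% to 100% of a 7-day recording, a 20,160-fold range. With any higher threshold the range is smaller, but magnitude above it is still discarded. The central conclusion does not depend on which threshold is meant. It rests on reading burden as the amount of AF, which is the natural reading where the protocol lists it beside recurrence.

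**What to change.** In Section 10.5:

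1. Keep the Kaplan-Meier and time-to-event analyses for AF recurrence only, and remove burden from the time-to-event sentence.
2. Define AF burden as the percentage of monitored Holter time spent in AF, at 10 weeks and at 12 months separately.
3. State the comparison: the between-arm difference at each visit with a 95% CI, by a method suited to skewed data with many zeros. A bootstrap interval for the difference in means is one example.

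The Schedule of Events has no baseline Holter, so the comparison is between arms after ablation and not a change from baseline.

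The cost is a few lines of protocol or analysis-plan wording, using burden data that are already to be recorded. The downside is a wide interval and low power. The gain is an estimate of the quantity that the objective names. The wording should be settled before outcome data are seen by arm.

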Participants will be reimbursed their travel costs for travelling to and from the Atrium Health Centre, for the purpose of CREED AF exercise training visits. They will be reimbursed up to a maximum of £10 per visit to the Atrium Health Centre, which will cover the cost of travel (public transport or fuel) and parking. This can be claimed by the participant at the conclusion of each intervention period (e.g., end of prehabilitation and rehabilitation). We will aim to align hospital visits with standard of care, however if any additional visits to the hospital are required that are specifically for the purpose of the CREED AF study, then these travel visits will be reimbursed, after each visit. Participants will be required to keep a log of their travel expenses during their time in the study.

- 1. **Consent**

Prospective participants will be asked to confirm whether they have read and understood the PIS and will be encouraged to ask questions and be provided enough opportunities to discuss before deciding to take part in the study. Patients will be free to discuss the study with friends and family before reaching their decision.

After confirming the patient’s eligibility to take part, a qualified member of the research team, who has received training in obtaining informed consent, will obtain consent. Informed consent will be obtained prior to the participant undergoing procedures that are specifically for the purposes of the CREED AF study and out-with standard routine care at UHCW. The participant will be able to refuse to participate in the study without giving any reasons and this will not affect their standard treatment in any way.

If informed consent is initially obtained remotely e.g., consent statements agreed over the phone, the participant will be asked to counter sign their consent form on their first study visit to the hospital before starting any assessments. A copy of the signed consent form will then be provided to the participant.

The consent procedure will be undertaken by a delegated member of the research team and will involve:

- Discussion between the potential participant and an authorised individual who is knowledgeable about the research and about the nature and objectives of the trial and possible risks associated with their participation.

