*Programme Design*: Participants randomised to the CREED AF intervention can immediately join existing cardiopulmonary rehabilitation exercise programmes rather than waiting for the recruitment of sufficient numbers to form a discrete group of trial participants.

Individual assessment and exercise familiarisation

*Individual assessment*: A 1-to-1 online appointment with a CREED AF ‘practitioner’ (specialist cardiopulmonary clinical exercise physiologist or physiotherapist). Participants will undergo an ‘assessment,’ as per standard practice in UK cardiopulmonary rehabilitation programmes, to assess medical history, medication, and discussion of participant goals, expectations, fears, and concerns.

*Exercise prescription*: The CREED AF practitioner will prescribe a tailored, individualised exercise programme within pre-specified parameters, as outlined in the information sheet. Clinical information, data from the exercise assessment, and patient centred goal setting will be used to devise a safe and effective exercise prescription. There are no accepted guidelines for exercise training in patients due for ablation. Our intervention will be individualised and based on existing evidence in similar populations, our PPI sessions, and our centres’ expertise in the provision of exercise for clinical populations.

*Familiarisation*: Exercise will be delivered on a rolling basis, so a participant can immediately join a pre-existing cardiopulmonary exercise group that is at a similar physical level to them. During the first week of the programme, the clinical staff will assess their capability to carry out the prescribed exercise. Following this, the exercise that the participant is undertaking could be altered slightly to better suit their physical capabilities. The familiarisation period will enable participants to build confidence, whilst CREED AF practitioners refine and optimise the exercise prescription.

Exercise Programme (2-3 times/week for 6-8 weeks, pre- and post-ablation)

Exercise training will be facilitated by a trained CREED AF practitioner using:

1. Participant manual with details of the exercise programme, instruction on safe and effective exercise, and a logbook to self-record completed exercise. These materials will be provided to participants at the start of the intervention.

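### The patient-cost window in Section 10.7 starts at ablation, so prehabilitation travel and time fall outside the secondary economic analysis; reimbursed travel after ablation may also be under-recorded

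*Protocol*

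**What the plan says.** - **Perspective and window (protocol, Section 10.7, opening paragraph).** The primary perspective is NHS and PSS, over a one-year horizon, "with secondary analyses including additional patient costs accruing over the 12 months period post ablation".
- **Healthcare costs (Section 10.7, Resource use and costs).** Total healthcare costs run from baseline to month 12 and include those due to the intervention. Attendance at both the pre- and post-ablation components is recorded and costed.
- **Patient costs (same paragraph).** The text says that "related costs incurred by the patient (e.g. out-of-pocket expenses and time-related costs) will be captured using a resource use measure (RUM").
- **Programme (Section 9, Intervention Group).** "Exercise Programme (2-3 times/week for 6-8 weeks, pre- and post-ablation").
- **Reimbursement (Section 9, Payment).** Travel "for the purpose of CREED AF exercise training visits" is repaid: "They will be reimbursed up to a maximum of £10 per visit to the Atrium Health Centre". On timing, "This can be claimed by the participant at the conclusion of each intervention period". Travel is also repaid "if any additional visits to the hospital are required that are specifically for the purpose of the CREED AF study". Finally, "Participants will be required to keep a log of their travel expenses during their time in the study".
- **Instrument (Schedule of Events).** The Resource Use Questionnaire is due at ablation, at the follow-up after rehabilitation and at month 12.

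**The concern.** The two cost streams in Section 10.7 start at different times. The cost of providing prehabilitation is counted, but the patient's cost of attending it is not, because it arises before the patient-cost window opens. Controls have no exercise sessions; before ablation they have one 30-minute education session, which may be remote. The omission is therefore almost wholly in one arm and lowers the intervention's cost in the analysis meant to show the patient's burden.

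Reimbursement raises a related question for the travel that is counted. A repaid expense is, on the ordinary meaning, no longer out of pocket. The payment appears in the protocol only as participant reimbursement, not as part of the programme. Claims fall at the end of each intervention period, close to the questionnaire dates, so some patients may answer before being repaid and others after. The protocol does not say how the payment is to be treated. Any net reporting of exercise travel can lower costs only in the intervention arm.

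**Working it through.** The protocol states no patient-cost figure, so there is nothing to reproduce. The check compares the windows and then bounds the sums.

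**1. Windows side by side**

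| Item | Start | Covers prehabilitation? |
| --- | --- | --- |
| Healthcare and intervention costs | Baseline | Yes |
| Patient costs, secondary analysis | Ablation | No |
| Resource Use Questionnaire | First completed at ablation | It can, by looking back |

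**2. Sessions per phase.** Sessions per week × weeks: 2 × 6 = 12 to 3 × 8 = 24. Section 9 defines compliance against 12 sessions per phase, with 8 counting as complete.

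**3. Travel left out by the window (prehabilitation phase).** Sessions × in-person share × £10. The share is not given; the protocol expects a mix of centre and online sessions.

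| Assumed in-person share | 12 sessions | 24 sessions |
| --- | --- | --- |
| 100% | £120 | £240 |
| 50% | £60 | £120 |
| 25% | £30 | £60 |
| 0% | £0 | £0 |

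A patient attending only 8 sessions, all in person, gives 8 × £10 = £80. Here £10 is a working value: it is the most that is repaid, not the most that a visit can cost.

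**4. Time left out by the window.** The Methods section gives one-hour exercise sessions and three 30-minute education sessions before ablation. That is 12 × 1 + 3 × 0.5 = 13.5 hours to 24 × 1 + 3 × 0.5 = 25.5 hours per intervention patient, before travel time, against 0.5 hours in controls. Session time does not shrink when sessions are online. The protocol gives no value per hour, so none is applied.

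**5. Travel possibly hidden by net reporting (rehabilitation phase).** Sessions × in-person share × £10, if the patient reports net of reimbursement. The table in step 3 applies again: at most £120-£240, and £0 if spending is reported gross or the log is used to add it back. Here £10 is a true ceiling, since anything above it stays with the patient.

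**6. The two parts together.** At £10 per visit, all sessions in person and all patients reporting net: £120 + £120 = £240 to £240 + £240 = £480 per intervention patient. At an assumed 50% in person: £120-£240.

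**The case against.** Several points on the other side have force.

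- **Net reporting is not established.** A reader might infer that the analysis certainly understates exercise travel, or that reimbursement alone hides £240-£480. The documents do not support either. Nothing says that expenses are reported net, and patients pay first and claim later, so gross reporting is plausible. While the window stays as written, reimbursement can affect only the post-ablation half. This part of the point is conditional.
- **The log may be used.** A reader might also infer that the travel log is excluded from the analysis. The protocol is silent; it neither links the log to Section 10.7 nor rules it out.
- **Patient costs are wider than out-of-pocket expenses.** Time-related costs are named and the list is illustrative. The phrase about related costs can be read as tied to other NHS care, and attendance is costed in its own sentence. That sentence neither includes nor excludes patient travel, so it does not settle the matter.
- **Net or gross could be left to an analysis plan or to questionnaire instructions.** That is fair for the reimbursement rule. It does not answer the window, which the protocol states.
- **The one-year horizon and the ablation-visit questionnaire.** The horizon might explain a post-ablation start, but the same section counts healthcare costs from baseline. The questionnaire at ablation suggests that earlier costs will be collected; the stated window then leaves them unused.

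**Conclusion.** The window is a fault in the stated plan. Followed as written, Section 10.7 drops the patient's travel and time for prehabilitation, a burden that falls on the intervention arm, and so favours CREED AF in the secondary analysis. At £10 per visit and full attendance, the omitted travel is £120-£240 per intervention patient if every session is in person and £60-£120 at an assumed 50%; it is £0 if every session is online. Session time is omitted in every case.

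The reimbursement effect is a possible addition of £0 to £120-£240, depending on the in-person share, on how often the cap is reached and on whether patients report net. No effect on the cost per QALY can be worked out from the document. The primary NHS and PSS result is not affected, so this is a worthwhile correction to a secondary analysis and does not threaten the main economic conclusion.

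**What to change.** In Section 10.7:

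1. Count patient costs from randomisation (baseline) to 12 months post ablation, matching the start used for healthcare costs, and reword the horizon to agree. Use the questionnaire already scheduled at ablation for the prehabilitation phase.
2. Value travel and parking for intervention sessions gross of trial reimbursement, from the travel log and the attendance record, for both phases.
3. Tell participants to leave trial-reimbursed exercise travel off the resource-use questionnaire, so that it is counted once.
4. Exclude travel made only for research assessments, in both arms.

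Make these changes together. Moving the window alone would bring prehabilitation travel into the analysis but expose it to the same net-reporting doubt. The questionnaire instruction should be settled before data are collected, because mixed net and gross answers cannot be reliably separated from the questionnaire alone.

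The cost is a few sentences and the entry of a log that participants already keep. The secondary cost-effectiveness ratio may become slightly less favourable to the intervention.
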